### Outcomes

The primary outcome is the change in WEMWBS score between the baseline assessment (M0) and the end of the 3-month cycle (M3), calculated using the formula ((score M^*n* + 1^ – score M^*n*^)/((score M^*n* + 1^ + score M^*n*^)/2)) × 100 [21, 26], expressed in percentage. Mean values and standard deviations will be used to define quantitative variables. The secondary outcomes are (1) the changes in WEMWBS scores between M0 and M1, M0 and M2, M0 and M9, and M0 and M15; (2) the mean WEMWBS scores before and after workshops in the intervention group at M0, M1, M2, and M3; (3) the changes in CESAM scores and its distribution of frailty categories (vigorous versus mild, moderate, and severe frailty) between M0 and M1, M0 and M2, M0 and M3, M0 and M9, and M0 and M15 [23]; (4) the change in EQ-5D scores, including VAS scores, between M0 and M1, M0 and M2, M0 and M3, M0 and M9, and M0 and M15 [25]; (5) the frequency of planned and unplanned physician visits, ER visits, and hospital admissions at M1, M2, M3, M9, and M15 [14, 16]; and (6) the changes in mean values of heart rate, daily steps, an sleep duration, and sleep phases, expressed in percentages, between M0 and M1, M0 and M2, and M0 and M3 for the subset of participants with recordings of these physiological measures. All changes will be expressed in percentages as mean values and standard deviations.

The number of workshops attended during the 3-month cycle of intervention is used to assess compliance with the participatory art-based activity. Compliance is defined as having attended at least 10 (83.3%) of the 12 workshops. If a participant attends a workshop for at least 1 h, they are considered to have attended a full workshop. If not, they are recorded as absent.

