First, the computer proficiency questionnaire (CPQ), which assesses respondents’ ability to use a computer, is performed in paper format [22]. Its scores range from 5 (i.e., never tried) to 30 (i.e., can do very easily). Second, socio-demographic characteristics including age, sex, and place of living are recorded using the CEEXLO web platform. Third, frailty is assessed with the digital short form of a self-administered questionnaire: The Centre of Excellence Self-AdMinistered questionnaire (CESAM, Table 2) [23]. This questionnaire is filled out by participants under the supervision of the principal investigator’s representatives. The 20 items that make up the CESAM explore several domains, including weight loss and its magnitude; polypharmacy, defined as a number of therapeutic classes taken on a daily basis ≥ 5; vision, hearing, and memory problems; use of home support (i.e., family, friend, and/or professional); the 6-item activities of daily living (ADL) scale and the 4-item instrumental activities of daily living (IADL) scale [24]; mood, assessed using the question, “How do you feel today?” with three possible answers (happy, unhappy, and neither one nor the other); practice of regular physical activity (e.g., walking and bicycle), defined as at least 1 h per week in the past month; and history of falls in the past 12 months. Each CESAM item is close-ended (i.e., yes, no, or choose a specific answer). Automatically, two scores are calculated: (1) a frailty score, ranging from 0 (i.e., best health and functional condition) to 18 (i.e., worst health and functional condition) and (2) a categorization of frailty into one of four stages (vigorous with a score between 0 and 3, mild frailty with a score between 4 and 7, moderate frailty with a score between 8 and 12, and severe frailty with a score above 12). Fourth, EuroQol-5D (EQ-5D) is used to assess participants’ quality of life [25]. This assessment is comprised of two parts. The first is a questionnaire containing five questions coded from 1 (i.e., no issue) to 5 (i.e., worst issue), resulting in total scores ranging from 0 (i.e., no issue) to 25 (i.e., worst issue). The second part of EQ-5D is a visual analog scale (VAS) that explores how good or bad participants perceive their health to be. This scale ranges from 0 (i.e., worst health a participant can imagine) to 100 (i.e., best health a participant can imagine). Fifth, the Warwick-Edinburgh Mental Well-Being Scale (WEMWBS) is used to assess mental well-being [26]. This questionnaire consists of 14 positively worded items with five response categories that cover several aspects of positive mental health. Its scores range from 14 (i.e., none of the time) to 70 (i.e., all the time).

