### Data analysis

Analyses will be performed (1) with the intention to treat for all enrolled participants randomized into two groups (i.e., intervention versus control) and (2) per protocol (i.e., removing data from participants who were not compliant with the protocol) for participants who will be entirely assessed through an 83.3% (i.e., participants who attended 10 on 12 workshops) compliance to the intervention. Analyses will be done through the SPSS Software (version 23.0; SPSS, Inc., Chicago, IL). Missing data will be taken into account with regression imputation. Data will be imputed only if the percentage of participants with missing data is under 10%. The continuous variables’ distributions will be studied (mean, median, mode, minimum, maximum, confidence interval around mean, standard deviation). For the categorical variables, frequencies will be calculated. First, the participants’ baseline characteristics (age, sex, etc.) will be described for each group and compared (i.e., intervention versus control) using parametric and non-parametric tests according to variables’ distribution. Pearson’s chi-square tests (or Fisher’s exact tests) will be used for qualitative variables. For quantitative variables, the statistical tests used will be unpaired *t* tests or non-parametric Mann-Whitney *U* tests for comparing 2 groups, as appropriate.

Second, group comparisons of changes (i.e., ((score M^*n* + 1^ – score M^*n*^)/((score M^*n* + 1^ + score M^*n*^)/2)) × 100) in outcome values between M0 and M1, M0 and M2, M0 and M3, M0 and M9, and M0 and M15 will be performed using repeated measures tests as appropriate. The global significance limit will be set at 0.05 and all tests will be bilateral. In addition to this univariate analysis, a multivariate analysis will be performed to determine the effect of the intervention while adjusting for age, sex, number of medications taken daily, and CPQ score. These adjusted variables are covariates that may influence the relationship between outcome measures (i.e., well-being, quality of life, and frailty) and the participatory art-based activity intervention.

Third, to identify the outcomes with the highest magnitudes of change (i.e., greater effect attributable to the intervention), we will graph the mean difference of each outcome that is significantly different when comparing intervention group participants to those in the control group. Results will be presented as forest plots.

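### The percent-change formula is undefined or fixed at ±200% for the CESAM frailty score whenever a participant scores 0, its best value

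*Protocol article*

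**What the plan says.** Outcomes defines the primary endpoint, the M0 to M3 change in WEMWBS, by a symmetric percent formula: later score minus earlier score, divided by the mean of the two, times 100. The same section lists as a secondary outcome "the changes in CESAM scores and its distribution of frailty categories (vigorous versus mild, moderate, and severe frailty", from M0 to each later visit, and closes its list with "All changes will be expressed in percentages as mean values and standard deviations".

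Data analysis writes the formula out again, this time for group comparisons of changes "in outcome values between M0 and M1, M0 and M2, M0 and M3, M0 and M9, and M0 and M15". It is not restricted there to WEMWBS.

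Baseline assessment describes CESAM as giving "a frailty score, ranging from 0 (i.e., best health and functional condition) to 18 (i.e., worst health and functional condition"; scores of 0 to 3 count as vigorous. WEMWBS runs from 14 to 70. For EQ-5D, five questions are each coded 1 to 5, "resulting in total scores ranging from 0 (i.e., no issue) to 25 (i.e., worst issue").

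The article gives no rule for zero scores and no other measure of change for the CESAM score.

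**The concern.** A measure that divides by the mean of two scores needs a scale that stays clear of 0. WEMWBS does. CESAM does not, and its 0 is the best possible health, within the vigorous band.

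Low scores are plausible in this trial. Recruitment is by email to museum visitors aged 65 and over, and people with major disabilities or major neurocognitive impairment are excluded. If the intervention reduces frailty as hypothesised, it moves scores towards the region where the measure breaks down.

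At stake is the score-based comparison of frailty, one of the outcomes named in the objective. Some valid pairs of scores would have no value. Others would take an extreme value unrelated to the size of the change and weigh heavily on the mean and standard deviation. The planned graph that identifies the outcomes with the largest changes would also be affected: one CESAM point can give ±200%, while WEMWBS cannot exceed ±133.3% across its whole range.

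**Working it through.** **Inputs.** Formula: Outcomes and Data analysis. CESAM 0 to 18, WEMWBS 14 to 70 and the EQ-5D item coding: Baseline assessment. The plan states no figure of its own on this point, so there is none to reproduce.

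**Formula.** For an earlier score a and a later score b, f(a,b) = (b − a) / ((a + b)/2) × 100.

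**CESAM (higher is worse).**
- f(0,0) = 0/0, undefined.
- If only a is 0: f(0,b) = b/(b/2) × 100 = +200. So 0 to 1, 0 to 3, 0 to 10 and 0 to 18 all give +200%.
- If only b is 0: f(a,0) = −a/(a/2) × 100 = −200. So 1 to 0 and 18 to 0 both give −200%.
- One point worse gives +200% from 0, +66.7% from 1, +40.0% from 2, +28.6% from 3, +9.5% from 10 and +5.7% from 17.

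**Reversal of sign.** Take one participant who goes from 10 to 5 and another who goes from 0 to 1.
- Percent: f(10,5) = −5/7.5 × 100 = −66.7 and f(0,1) = +200. The mean is (−66.7 + 200)/2 = +66.7%, a worsening.
- Points: (−5 + 1)/2 = −2, an improvement.

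**Contrast with WEMWBS.** The extreme is f(14,70) = 56/42 × 100 = 133.3%. The denominator is never below 14, so the primary outcome is always defined.

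**How many participants.** The document gives no CESAM distribution, so this part is an assumption. Let each person's expected score be gamma with shape 2 and mean μ, the two visits be independent Poisson counts given that person, and there be no true change. Then:
- P(0 at both visits) = (1 + μ)^−2
- P(0 at exactly one visit) = 2 × [(1 + μ/2)^−2 − (1 + μ)^−2]

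| Assumed mean μ | Undefined (0/0) | Exactly ±200% |
|---|---|---|
| 1 | 25% | 39% |
| 2 | 11% | 28% |
| 3 | 6% | 20% |
| 5 | 3% | 11% |

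A simulation of the same model, run for means 2, 3 and 5, agrees.

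**EQ-5D range.** Five items coded 1 to 5 sum to at least 5 × 1 = 5 and at most 5 × 5 = 25. The stated minimum of 0 cannot occur. On 5 to 25 the formula is always defined: one level worse from the best state is f(5,6) = 1/5.5 × 100 = 18.2%.

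**The case against.** **The frailty outcome has two parts.** The distribution of frailty categories uses the raw score and is untouched by the formula. The earlier single-arm study, as the Background and Discussion describe it, based its physical-health finding on those categories. This stands. A reader might infer that the whole frailty result would be untrustworthy, but the document does not support that.

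**The handling of 0/0 could be a convention in an analysis plan.** Counting 0 to 0 as no change would be natural. A reader might infer instead that the healthiest, stable participants will be dropped or imputed; the article does not say so. The point stands for 0/0, but such a convention leaves the ±200% plateau as it is. Nor is the formula an omitted detail: the article fixes it. The words allowing flexibility in Data analysis refer to the choice of repeated measures test, not to the measure of change.

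**The size is assumed.** Means of 1 to 3 lie within the vigorous band, yet the Discussion describes the programme as focused on early frailty, and mild frailty is 4 to 7. At a mean of 5 the shares fall to about 3% and 11%. Many CESAM items change slowly, which would give more 0/0 pairs and fewer values at ±200%. How often a score is exactly 0 is unknown. All of this stands, so the table is only an illustration.

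**EQ-5D does not fail as collected.** A reader might infer the same breakdown from the stated range starting at 0. That would need a rescaling to 0 that the article does not describe. What remains is a misstated range.

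**Unequal percentages alone are no fault.** Any relative measure makes 1 to 2 larger than 10 to 11. That is fair; the defect is the behaviour at 0.

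**Conclusion.** The point holds for the change in CESAM score. As written, the formula has no value for one valid pair of scores, ignores the size of the change for every pair with a single 0, and can give a mean whose sign is opposite to that of the mean point change. These results follow from the formula and the stated scale and need no assumption. How many participants are affected does: roughly 3% to 25% undefined and 11% to 39% at ±200% under the model above, with the true shares unknown.

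The primary outcome and the frailty categories are not affected. No fault is shown for the EQ-5D visual analogue scale or the physiological measures, so nothing here argues for removing the percent formula from them. The EQ-5D sum range is a separate, minor misstatement. This should be fixed, as a defect in one component of a secondary outcome.

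**What to change.** In Outcomes and Data analysis, exempt the CESAM score from the percent formula. Compare groups on the absolute change in points or, preferably, on the follow-up score adjusted for the baseline score. Both are defined for every pair: 0 to 0 is 0, 0 to 1 is +1, 0 to 10 is +10 and 3 to 0 is −3 points. Leave the comparison of frailty categories as it is.

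In Baseline assessment, correct the EQ-5D sum range to 5 to 25, and score it on that range if the percent formula is kept for it.

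The cost is a wording change in three sections. It needs no new data and does not touch the sample size, which rests on WEMWBS. Making it before the data are analysed also avoids choosing how to treat zeros once the results are known.

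### The percent-change formula is prescribed for the CESAM frailty score, which starts at 0, where the formula is either undefined or fixed at ±200%

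*Protocol article*

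**What the plan says.** The Outcomes section introduces the formula for the primary outcome, the change in WEMWBS from M0 to M3. It then lists as a secondary outcome "the changes in CESAM scores and its distribution of frailty categories", from M0 to each of M1, M2, M3, M9 and M15, and closes with "All changes will be expressed in percentages as mean values and standard deviations".

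The Data analysis section repeats the formula for the between-arm tests: "group comparisons of changes (i.e., ((score M^*n* + 1^ – score M^*n*^)/((score M^*n* + 1^ + score M^*n*^)/2)) × 100) in outcome values", for M0 against each later visit. Neither section makes an exception for any scale.

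The Baseline assessment section describes CESAM as "a frailty score, ranging from 0 (i.e., best health and functional condition) to 18", where 18 is the worst condition. The best category is "vigorous with a score between 0 and 3", so 0 is an attainable score inside that category. The same section gives WEMWBS a range of 14 to 70, the EQ-5D VAS a range of 0 to 100, and the EQ-5D total a stated range of 0 to 25.

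No rule is given for a zero score or a zero denominator.

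**The concern.** The formula suits WEMWBS, which cannot be lower than 14. Applied to a score that starts at 0, it behaves badly exactly where the healthiest participants sit. Low scores are plausible here: participants are recruited by email from museum visitors, people with major disabilities, gait disorders or major neurocognitive impairment are excluded, and many CESAM items ask about needing help.

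Frailty is the trial's measure of physical health. If its score change is summarised and tested as a mean percent change, the result gives most weight to small moves among people with almost no frailty, and least weight to moves among those with more. The third analysis step also compares outcomes by magnitude of change in forest plots, where a CESAM percentage would not be comparable with a WEMWBS percentage.

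**Working it through.** **Inputs.** The formula is from Outcomes and Data analysis; the scale ranges and category limits are from Baseline assessment. The article gives no CESAM result on this scale, so there is no stated figure to reproduce.

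**Formula.** With *a* the M0 score and *b* the later score, f(a, b) = (b − a) / ((a + b)/2) × 100 = 200 (b − a)/(a + b).

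**Behaviour at 0.**
- f(0, 0) = 200 × 0/0: undefined.
- f(0, b) = 200 b/b = +200% for every b from 1 to 18.
- f(a, 0) = −200 a/a = −200% for every a from 1 to 18.

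**Behaviour elsewhere on CESAM.**

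| Move | Points | Percent change |
|---|---|---|
| 0 to 1 (stays vigorous) | +1 | +200% |
| 1 to 2 (stays vigorous) | +1 | +66.7% |
| 3 to 4 (vigorous to mild) | +1 | +28.6% |
| 7 to 8 (mild to moderate) | +1 | +13.3% |
| 17 to 18 | +1 | +5.7% |
| 4 to 3 (mild to vigorous) | −1 | −28.6% |
| 12 to 8 (stays moderate) | −4 | −40% |

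A 0-to-1 move within the vigorous category counts 200/28.6 = 7 times a 3-to-4 move that crosses into mild frailty.

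**Can the sign differ from the change in points?** Take ten people going 7 to 4 and three going 0 to 1 (constructed).
- f(7, 4) = 200 × (−3)/11 = −54.5%.
- Mean in points: (10 × −3 + 3 × 1)/13 = −27/13 = −2.08, an improvement.
- Mean percent: (10 × −54.545 + 3 × 200)/13 = 54.55/13 = +4.2%, a worsening.

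On the percent scale 545.45/200 = 2.7 such 0-to-1 moves cancel the ten improvements. On the point scale it would take 30.

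**How often could this occur?** The article cannot answer this, so the following is an assumption with its range. Each visit's score is a shared Poisson part (70% of the mean) plus a visit-specific Poisson part (30%), capped at 18, with no true change.

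| Assumed mean CESAM | Undefined (0 to 0) | At ±200%, of defined values | Share of sum of squares from the ±200% values |
|---|---|---|---|
| 1 | 27% | 26% | 90% |
| 2 | 7% | 13% | 75% |
| 3 | 2% | 6% | 55% |
| 5 | 0.1% | 1% | 22% |

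**Other scales.** For WEMWBS the formula is always defined, and its extremes are f(14, 70) = 200 × 56/84 = +133.3% and the reverse, −133.3%. The EQ-5D VAS and the EQ-5D total as stated include 0 and so share the weakness in principle. Five items each coded from 1 would sum to at least 5, so the stated minimum of 0 for the total does not follow from a simple sum. If 5 is the true minimum, the formula is defined for that score.

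**The case against.** The best case on the other side is that this is a secondary outcome. The primary outcome and the sample size rest on WEMWBS, where the formula is always defined. Frailty also has a second route, since the same outcome item includes the distribution of categories, and the earlier study's frailty finding was described as proportions. A 0-to-0 participant could be coded as no change by a simple convention in an analysis plan that is not shown. All of this stands and limits the seriousness. It does not remove the point: coding 0/0 as 0 leaves the ±200% values and the unequal weighting in place, and using the formula for CESAM is a stated choice.

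Four stronger readings are tempting but not supported.
- A reader might infer that 0-to-0 participants become missing, and are then imputed or push the trial past the 10% limit. The article says "Missing data will be taken into account with regression imputation", but both scores of such a participant are observed, and nothing says that an undefined ratio counts as missing.
- A reader might infer that the frailty-category outcome cannot be analysed. It can be compared as proportions without the formula, and the article provides frequencies for categorical variables.
- A reader might attribute a large loss of power to the formula by comparing an unadjusted test of percent change with a baseline-adjusted analysis of points. That contrast changes two things at once. In simulations under assumed distributions (63 per arm, overdispersed counts with mean 2 to 4, 25% lower score), the percent scale alone cost 14 to 23 percentage points of power, and adjusting for M0 accounted for a further 13 to 19. No CESAM distribution in the article supports either range.
- A reader might take the sign reversal as likely. The example shows only that it is possible.

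**Conclusion.** The concern holds for the CESAM score. The article prescribes a change formula that has no value for a participant at 0 on both visits, that gives ±200% for any move from or to 0 regardless of size, and that gives much smaller values to moves higher on the scale. This is exact arithmetic on the article's own formula and range, and rests on no assumption. That the mean percent change can be dominated by participants near 0, and can differ in sign from the mean change in points, follows from it.

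The size of the distortion in this trial is unknown. It depends on how many participants score at or near 0: under the assumed means of 1 to 5, undefined values range from 27% down to 0.1%. The documents therefore do not support saying that the frailty result will be wrong, only that the stated measure can mislead. The WEMWBS primary outcome and the frailty-category proportions are unaffected. This should be fixed, as a secondary-outcome matter.

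**What to change.** In Outcomes and Data analysis, limit the percent formula to scales that cannot reach 0, such as WEMWBS. Exempt CESAM and the EQ-5D scores whose stated range includes 0, and confirm the true minimum of the EQ-5D total.

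For the exempted scores, analyse the raw score at each visit with the M0 score as covariate, and report the between-arm difference in points with a 95% CI. State that frailty categories are compared between arms as proportions.

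The M0 scores are already collected from all participants, so the change needs only wording and no new data. The small loss is that these outcomes no longer share a percent unit with WEMWBS, including in the forest plots. A standardised difference could be used there instead. The change should be made before unblinded data are examined, so that the handling of zeros is not chosen after seeing results.

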### Data safety and storage

For the duration of this RCT, the principal investigator (PI) and representatives collect and store personal identifiable information about participants in a digital file for the collection of clinical and physiological data and a paper copy of the signed consent form. Only information needed for the study is collected. The digital information is stored on the secured medical webserver of RUISSS McGill Center of Excellence on Longevity. Data are downloaded as an Excel file from this webserver using a secured link on a secured computer located in a locked room in the Division of Geriatric Medicine of the Jewish General Hospital. There is a double lock system on the computer allowing data access, with separate passwords to access the computer and to open the database. The printed and signed consent forms are also stored in a locked room in the Division of Geriatric Medicine of the Jewish General Hospital, in a locked cabinet. The information collected from this research is not be used for other research purposes and it will be destroyed 10 years following the end of recruited individuals’ participation in this study. If the PI leaves the institution, administrative and ethics rules applicable in Quebec and the CIUSSS West Central Montreal are followed to manage the data. All personal information collected during the study remains confidential within the limits of the law. To protect participant identity, the name and other identifying information are replaced by a code (numerical incremental code), which is the only information about participants to which the PI and representatives have access during the study. Only the project manager is able to link participant codes to participant identities. No information that discloses participant identities is communicated. The coded information may be communicated to Health Canada in the case of an audit. The participants’ coded study information and the participants’ consent forms are also destroyed 10 years following the end of their participation in this study, as consent forms are part of participants’ research file and follow the same rules of recorded data in this study.

